### Economic analysis

Economic analysis and reporting will be consistent with published frameworks [47], including the Consolidated Health Economic Evaluation Reporting Standards (CHEERS) guidelines for reporting of health economic research [48]. The primary economic analysis within this study will analyse the difference in total direct costs in Australian dollars (at 2016 prices) from the health-service perspective. Total per-episode costings will be obtained, as well as individual item costs to identify the elements of patient care that underpin any significant cost differences between the two intervention models. Costings will include the 90 day post-discharge period to capture outpatient specialist, allied health, pathology and radiology services, as well as any readmission to hospital. Only costs incurred directly by Western Health will be included in this analysis.

A cost-effectiveness analysis from the health-service perspective will also be completed, with the incremental cost for each life year saved to be compared between the community-acquired pneumonia service best-practice intervention and usual care groups. This analysis will consider inpatient costs and mortality to 90 days following the original admission to hospital. Depending on the outcomes of preliminary analysis, appropriate analysis of uncertainty, such as use of non-parametric bootstrapping methods to calculate 95% confidence intervals with a corresponding cost-effectiveness plane and acceptability curves, will be explored [49].

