#### At 30 and 90 days following presentation to the emergency department (outcome measures)

Mortality, institutional readmission within 30 and 90 days and total institutional costs incurred at 30 and 90 days will also be extracted from the institutional data warehouse and linked to the study dataset as described previously.

Any adverse event or complication (as defined in Table 2) that requires re-presentation to hospital noted in the electronic medical record within 30 days of initial arrival in the emergency department will be recorded.

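### The cost-effectiveness ratio is described on inpatient costs while the primary economic analysis counts total direct costs, so the two results can diverge by definition alone

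*Protocol article*

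**What the plan says.** All of this is in the protocol article.

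- **Primary economic analysis (Economic analysis, first paragraph).** It "will analyse the difference in total direct costs in Australian dollars (at 2016 prices) from the health-service perspective". On scope and window: "Costings will include the 90 day post-discharge period to capture outpatient specialist, allied health, pathology and radiology services, as well as any readmission" to hospital. On payer: "Only costs incurred directly by Western Health will be included in this analysis".
- **Cost-effectiveness analysis (Economic analysis, second paragraph).** "A cost-effectiveness analysis from the health-service perspective will also be completed", with an incremental cost per life year saved. On scope and window: "This analysis will consider inpatient costs and mortality to 90 days following the original admission to hospital".
- **Data extraction (Data collection, 30- and 90-day outcome measures).** Under a heading that counts from emergency presentation, "total institutional costs incurred at 30 and 90 days will also be extracted from the institutional data warehouse", alongside mortality.

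No reason is given for the narrower cost description in the second analysis.

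**The concern.** Two analyses with one stated perspective should normally draw on one set of costs, or say why they do not. Here the article itself fixes both scopes, and they differ, so this is not a detail left to a fuller document.

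The intervention is meant to shorten hospital stay. If some care then moves from the ward to outpatient services run by Western Health, the primary economic analysis records that cost and the ratio does not. The reverse could also happen. Either way, a reader comparing the two results could not tell a real finding from an effect of the definitions.

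The time windows add a second mismatch. A cost window that ends 90 days after discharge has a length that depends on the primary outcome, whereas mortality is counted over 90 days from the start of the episode.

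The Discussion makes continuation of the service depend on financial as well as clinical results, so the economic outputs are meant to inform a decision.

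**Working it through.** The article states no cost figures, so there is nothing to reproduce. The check compares the texts and adds simple algebra.

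**1. Scope and window side by side**

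| | Primary economic analysis | Cost-effectiveness ratio | Data extraction |
|---|---|---|---|
| Perspective | Health service | Health service | Institution |
| Costs | Total direct, including post-discharge outpatient items and readmission | Inpatient | Total institutional |
| Window | To 90 days after discharge | To 90 days from original admission | 30 and 90 days from emergency presentation |

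The extraction column shows that data availability does not explain the inpatient restriction.

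**2. Effect on the ratio**

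Let ΔC_in be the between-group difference in inpatient cost, ΔC_out the difference in post-discharge outpatient cost borne by Western Health, and ΔLY the difference in life years.

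- Ratio as written: ΔC_in / ΔLY
- Ratio on the primary cost scope: (ΔC_in + ΔC_out) / ΔLY
- Amount omitted: ΔC_out / ΔLY

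If ΔC_out = 0, the two ratios coincide. If outpatient cost is higher under the intervention, the ratio as written omits a cost of the service. If it is lower, the ratio omits a saving.

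**3. Illustration, on an assumption that is not in the document**

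Suppose the intervention saves an inpatient amount S per patient and a fraction f returns as Western Health outpatient cost. The net saving is S(1 − f), so the inpatient-only figure overstates it by 1/(1 − f):

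| Assumed f | 1/(1 − f) |
|---|---|
| 0% | 1.00 |
| 10% | 1.11 |
| 25% | 1.33 |
| 50% | 2.00 |

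The article gives no basis for choosing a value of f.

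**4. Windows**

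Measured from the start of the episode, a window ending 90 days after discharge lasts L + 90 days, where L is length of stay. The Background cites a two-day reduction in stay from an earlier trial of early mobilisation and early oral switch. With that reduction the intervention window would be (L − 2) + 90 days, two days shorter. Since L must be at least 2, the relative difference is at most 2/92 = 2.2%. This is small, but it is built into the definition and a fixed origin removes it.

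The extraction as described stops 90 days after emergency presentation. It therefore fits a fixed window and falls L days short of the post-discharge one.

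**5. Ambiguity in the sentence**

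The 90-day limit may govern both costs and mortality, or mortality alone. On the first reading, inpatient readmission costs within 90 days stay in the ratio. On the second, it is unclear whether they do.

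**The case against.** The case for leaving the text alone has several parts.

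- **The sentence does not say that only inpatient costs count.** This is true, but restriction is its natural meaning directly after a paragraph that lists outpatient items.
- **The ratio is an additional analysis, and Statistical methods defers secondary and sensitivity analyses to a detailed plan.** This limits how final the wording is, but does not reconcile the two scopes already stated.
- **Shifted costs do not leave the trial's evidence.** The primary economic analysis would show them, and individual item costs are obtained to explain differences. This stands and limits the consequence to the ratio and to its agreement with the primary economic result.
- **Obvious substitutes for ward days are treated as part of the stay.** Data collection at discharge counts sub-acute and rehabilitation care and hospital care at home within total length of stay. Inpatient readmissions also remain, on the first reading above. What clearly drops out is therefore narrower: outpatient clinic, allied health and diagnostic services after discharge. This stands too.
- **Emergency presentation and admission are nearly the same clock.** I agree. The difference that matters is between either of these and discharge.

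A reader might go further and infer that a move to outpatient care is the most likely cost effect of the intervention, or that the ratio will be wrong by a large amount per life year. The documents support neither. Nothing shows that such a shift will occur, or in which direction. A figure per life year would need an outpatient cost, a mortality difference and a rule for turning deaths averted into life years, and the article gives none of these.

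**Conclusion.** The inconsistency is real and lies in the current text: one perspective, two cost scopes, and a primary cost window whose length depends on the primary outcome. Read plainly, the ratio omits ΔC_out / ΔLY, so the two economic results can disagree through definition alone.

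The size cannot be stated from the documents, and it is zero if post-discharge outpatient costs do not differ between groups. The window effect is small: at most about 2.2% for a two-day difference in stay. The conclusion rests on reading the cost-effectiveness sentence as a restriction to inpatient costs, and on reading the extracted institutional totals as covering outpatient services, as the primary economic analysis requires.

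The trial's primary outcome analysis is untouched. The point is worth correcting because the correction is cheap.

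**What to change.** 1. In the cost-effectiveness analysis, define the numerator as total direct Western Health costs, inpatient plus outpatient, over 90 days from emergency presentation. This matches the extraction of costs and mortality already planned.
2. State the same fixed window for the primary economic analysis in place of the post-discharge one. Without this second change the two analyses would still not match.
3. Word the sentence so that the 90-day limit clearly applies to both costs and mortality, with readmissions included.
4. If the inpatient-only ratio is of interest, report it as a sensitivity analysis.

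The cost is a wording change to both economic analyses, with no new data. The primary cost window also loses some follow-up at its end, for each patient roughly as many days as the length of stay.

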### Data monitoring

Adverse events and adverse drug reactions that are considered to be associated with the delivery of the community-acquired pneumonia service protocolised interventions will be reported to the principal investigator within 72 hours. Patients receiving routine corticosteroids as a component of the community-acquired pneumonia service interventions will be reviewed daily and records will be kept of any hyperglycaemia requiring new insulin treatment. A log of adverse events and adverse drug reactions will be kept and reported to the project steering committee at quarterly meetings, and to the Melbourne Health Human Research Ethics Committee at 3 month intervals.

Serious adverse events and suspected unexpected serious adverse reactions will be reported to the Melbourne Health Human Research Ethics Committee within 72 hours. These may include (but are not limited to):Unexpected deathSerious drug-related adverse event (directly linked to either antibiotic or corticosteroid dose) where it is required that the drug is stoppedA fall with associated patient or clinician injury during physiotherapyPatient deteriorating clinically within 60 min of a physiotherapy session requiring a medical emergency team call or code blue (as defined by institutional procedures)

The project steering committee will meet quarterly to report enrolment numbers, protocol adherence or violations and adverse events and report these to the human research ethics committee. A data monitoring committee was not deemed necessary because outcome measures (e.g. length of stay) are (1) objective, (2) unambiguous and (3) collected through existing routine, validated measures (and therefore not prone to data integrity issues).

### Duration and timeline

It is anticipated that the study period will be completed in July 2017 and that data collection will be completed and analysed, and the manuscript prepared for submission, by December 2018. The final manuscript will be written in accordance with the relevant CONSORT statements and extensions [30].

Trial design and methods are summarised in Table 3.

**Table 3 Tab3:** World Health Organization Trial Registration Data Set for IMPROVE-GAP trial

Data category	Information
Primary registry and trial identifying number	www.ClinicalTrials.gov, NCT02835040
Date of registration in primary registry	22 May 2016
Secondary identifying numbers	Not applicable
Trial protocol version	This is Version 3 of the protocol and was enacted on 24 August 2016
Source of monetary or material support	The HCF Research Foundation (AU $300,000)
Primary sponsor	The HCF Research Foundation
Secondary sponsor	Not applicable
Contact for public queries	HK, [contact]
Contact for scientific queries	HK, [contact]
Public title	IMPROVing Evidence-based treatment Gaps and outcomes in community-Acquired Pneumonia (IMPROVE-GAP).
Scientific title	IMPROVE-GAP: Evaluating the impact of a new model of care designed to improve evidence-based management of community-acquired pneumonia
Country of recruitment	Australia
Health condition or problem studied	Community-acquired pneumonia
Intervention	Active comparator: Evidence-based bundle of care (specifically: corticosteroids, early mobilisation, guideline-compliance antibiotic and early switch to oral antibiotic therapy, malnutrition risk screening and targeted nutritional therapy) Placebo comparator: Usual inpatient care
Key inclusion and exclusion criteria	Ages eligible for study: ≥ 18 yrs Sexes eligible for study: Both Accepts healthy volunteers: No Inclusion criteria: All adults admitted to the institution under a general internal medicine unit with community-acquired pneumonia (meeting a standardised community-acquired pneumonia definition) Exclusion criteria: (1) patients where a decision is made to implement palliative care on admission; (2) existing enrolment in a clinical trial.
Study type	Type: Investigator-initiated, interventional, pragmatic, study Allocation: Concealed randomisation Intervention model: Stepped-wedge rollout Masking: Patient and assessor blinded Primary purpose: Treatment Phase: Phase IV
Date of first enrolment	01/08/2016
Target sample size	Minimum 640 patients
Recruitment status	Recruiting
Primary outcome measure	Hospital length of stay
Key secondary outcome measures	Inpatient mortality, 30 and 90 day readmission rates and mortality, ICU admission and ventilation, total clinical costings, protocol adherence, serious adverse events

## Discussion

IMPROVE-GAP will be the first RCT powered and designed to investigate a service-delivery approach to improving the translation of evidence into clinical practice in community-acquired pneumonia, one of the highest-burden conditions affecting health systems worldwide. Its stepped-wedge design is better suited than other RCT approaches to evaluating a health-service intervention in a ‘real-world’ operational context. It also has pragmatic advantages in that once the study is completed, the intervention has effectively been implemented in the health system in which it has been tested and, should the implementation be found to be financially and clinically effective, can then be continued indefinitely. It may therefore demonstrate the power of stepped-wedge trial designs to accelerate the ‘time to translation’ when implementing clinical trial evidence in routine clinical practice [21]. This has value both to patients, who benefit from improved outcomes and, if the intervention also has an efficiency dividend, to the health system. We acknowledge the possibility that, despite considering patients masked to allocation owing to the waiver of consent, that it is possible that some patients were aware of study interventions. However, we feel that the risk of selection bias was minimised, as allocation to treating unit was determined by established practice according to day of admission or previous admitting unit. Our design also aimed to minimise attrition bias (by using routinely available outcome measures, such as length of stay, clinical cost and inpatient mortality) although readmission rate may be susceptible to attrition bias, as readmission to other health services was not routinely available nor collected.

An extremely important aspect of our study design was the decision by our supervising human research ethics committee to grant a waiver of consent for this study. This approach required very careful deliberation by both the investigating team and the human research ethics committee and represents an important precedent for conducting health-service research of this type, especially as it will allow enrolment of a study population that is truly representative of a ‘real-world’ scenario, generalisable to the population of patients with community-acquired pneumonia in developed countries and health care systems where most patients are now elderly, with high rates of multimorbidity and complex care needs. We believe this will be vital for high-quality health-service research in the future, by enabling a robust means of prospectively measuring the effectiveness of new health-service interventions in representative populations. We also strongly believe that this approach is ethically justifiable, based on its use of routinely available data, application of an intervention based on best practice (supported by a high level of existing evidence) and its concordance with current official ethical guidelines for use of a waiver of consent. Nonetheless, we acknowledge that the approach represents a departure from existing conventional clinical trial designs and could still be considered controversial. In particular, there can be subjectivity and disagreement within the clinical and scientific community as to the quality and applicability of evidence from previous clinical trials. This may undermine our assertion that our intervention represents ‘best practice’, which is fundamental to our argument of ethical defensibility. It is also notable that many aspects of our intervention that we deemed well-supported by evidence are yet to be incorporated into official consensus guidelines. In particular, the most widely cited community-acquired pneumonia management guidelines are those of the Infectious Diseases Society of America; these have not been updated since 2007. We decided, however, that these have been superseded by more recent studies and that the most ethically defensible approach therefore was to provide our patients with the benefit of knowledge accrued from large RCTs and meta-analyses performed more recently. However, we acknowledge that there was potential for subjective interpretation as to how we assessed the existing body of evidence in its entirety. It is also possible that the evidence on which we based our interventions will, in turn, be superseded by subsequent clinical trials. For these reasons, it is therefore possible that human research ethics committees in other settings and who operate under different guidelines might decide to rule against granting a waiver of consent for a study of this type. Regardless, IMPROVE-GAP represents an important precedent that should be a starting point for ongoing discussions regarding the best ways to prosecute future health-service research, particularly translation of best practice, in this ethically complex and challenging environment.

## Trial status

The trial is ongoing and is actively enrolling.

## Abbreviations

CHEERS: Consolidated Health Economic Evaluation Reporting Standards
CORB: Confusion (acute), oxygen saturation ≤ 90%, respiratory rate ≥ 30 breaths per minute, blood pressure < 90 mm Hg (systolic) or ≤ 60 mm Hg (diastolic)
PCR: polymerase chain reaction
RCT: Randomised controlled trial
REDCap: Research Electronic Data Capture
SpO_2_: pulse oximetry oxygen saturation
TIDieR: Template for Intervention Description and Replication
